## Diet-induced weight loss intervention (group D)

Women randomised to diet only group will be prescribed a diet creating a mean energy deficit of 500 kcal/day during a weight reduction period of 10-14 weeks. This is assumed to produce a weight loss of 5-6 kg in total (approximately 0.5 kg per week). Diet composition and recommendations will be comparable to the baseline diet.

The weight reduction period, will be followed by a weight maintenance period of 2-6 weeks in which energy intake and energy expenditure will be balanced. The weight maintenance period starts as soon as the individual weight reduction goal is obtained (total weight loss of 5-6 kg), or in study week 19. From this time point until end of study, energy intake should meet the individual energy requirements for weight maintenance.

*Dietary counselling during the weight reduction intervention phase (see fig 1) will consist of:*

- Two individual 30 minutes individual sessions with a dietician. During the first session (week 6), individualised instructions are given on how to create the daily energy deficit of 500 kcal and perceived individual pitfalls will be discussed. The second session will take place at the end of the weight reduction phase in order to instruct the participant on how to maintain the reduced body weight.
- Five group sessions: In these one-hour sessions, participants in this treatment arm will be trained for self-management of body weight reduction and maintenance at the long run.
- Seven phone calls: the dietician will contact the participants by phone to evaluate body weight, motivate them and discuss diet adaptations if necessary.
- Completion of a food-record once during the intervention period. Participants will be instructed by the dietitian to record their daily food intake using a food-diary for 3 consecutive days (2 weekdays and 1 weekend day) De dietitian will provide feedback on energy and nutrient content of the reported intake

*Background principles and structure of the weight loss intervention:*

We use several theoretical models53-55 putting different emphasis on the key psychological processes of behavioral change. In accordance with these models, the following methods56-59 will be used to modify woman’s behavior depending on her individual characteristics and preferences:

- Self-monitoring of body weight and energy intake

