- Goal-setting: participants will be instructed to set specific (i.e. quantifiable) behavioral goals for the timeframe until the next session. The goals should be realistic, yet moderately challenging.
- Stimulus control: participants must identify stimuli and high risk-situations. They should develop their own controlling strategies, such as learning to shop carefully for healthy food, keeping high-calorie foods out of the house, limiting the times and places of eating, and consciously avoiding situations in which overeating occurs.
- Problem solving: participants should identify and self-correct problem areas related to their eating
- Relapse prevention: several skills to overcome setbacks and to cope with problems will be taught.

*Mode of delivery:*

The weight loss intervention is delivered by dieticians experienced in overweight treatment. Individual and group sessions are planned. Group sessions are supposed to provide a combination of social support and a healthy dose of competition. Group treatment is also more cost-effective than individual care60. Furthermore, there is evidence that group support might produce greater weight loss effects than individual counselling alone61. A family member or other support person may be invited to attend any or all sessions to increase social support62, 63.

*Intensity and duration of contacts:*

Frequent contact between participants and team members is proven to be a relevant success factor for weight reduction64. In most studies65 lifestyle modification training is provided weekly for an initial period of 16 weeks. In our programme, the contact frequency will be quite similar (see Figure 1). The dietary intervention will consist of 2 one-hour individual sessions, 5 one-hour group sessions and 7 phone calls. A recently published large randomised controlled trial in overweight adults showed that with this kind of dietary intervention relevant weight loss can be achieved. This study found an average weight loss of 7% of initial weight after six months66.

*Group sessions:*

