Group sessions will be conducted by a dietician using a structured curriculum in groups of 10 women. The nutritional education will include information on the importance of regular meal takings, the need for breakfast, the influence of snacking and grazing, a closer look at portion sizes and food labels, and the energy density of several food groups. Social support will be stimulated during the sessions using group discussion and reinforcement techniques. At each session, women review each others weight history and help each other generating strategies to cope with problems identified. Also personal feedback will be given by the dietician.

Lecture time will be kept to a minimum in favour of participants asking questions or discussing their pitfalls or achievements. Visits conclude with discussion of homework assignments for the coming weeks and the instruction not to change their habitual physical activity level.

*Protocol adherence:*

Adherence to the protocol will be determined during each phone call and individual/group meeting by examination of body weight and by energy intake estimated by the food-record and the dietician. Participants, whose weekly weight loss do not meet or exceeds the 0.5 kg/week goal for 3 consecutive weeks, will receive extra coaching and/or their diet will be adapted.

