Twice a week the participants of the combined exercise- plus diet-induced weight loss group will gather for a supervised exercise session for 60 minutes. The groups consist of 5-6 women. A physiotherapist who is extensively trained for the study will facilitate the standardised group sessions. Classes will start with a warming up. Then the training is continued with moderate-to-vigorous level of aerobic exercise (circuit training) on 60-90% of the peak heart rate (60-84% of VO2peak). The percentage of peak heart rate on which participants will train will increase gradually during the study programme (see table 1). The endurance training in week 9-14 will be a high-intensity interval training, with 30 seconds of intensive exercise and 60 seconds of active rest.  Exercise intensity was based on the guidelines of the American College of Sports Medicine, adapted for older woman70. Peak heart rate of each participant will be measured during a maximal exercise test. The participants will wear heart rate monitors to control their training intensity. They will also receive a badge with their target heart rates for a range of training intensities. The intensity and duration of the endurance training will be gradually inclined in the first weeks. Each training session will end with standardised strength exercises of the major muscle groups (see Tables 3a and 3b for an example of exercises; the type of exercise for a specific muscle group might be adapted to the facilities of the physiotherapist centre) and 5 minutes cooling down. The first week will be a run-in period for the strength exercises in which the technique of the exercises will be extensively instructed and practiced. Furthermore, in the first week the 20 repetition maximum (RM) (i.e. the maximum load that a muscle group can perform 20 repetitions of an exercise before becoming fatigued) will be determined for the different exercises (except for the abdominal exercises). This 20 RM will be the starting point for the strength training programme. To secure sufficient training load throughout the training programme, the 20 RM will be repeated at week 4; and a 15 RM will be determined at week 8 and 12.

Table 1. Content and composition of the group sessions

|  | **Time (min)** | **Intensity (% HF max for endurance part)** | | | | | |
| --- | --- | --- | --- | --- | --- | --- | --- |
|  |  | Phase 1 | | Phase 2 | | Phase 3 | |
| *Part of the session* |  | Wk 1-3 | | Wk 4-8 | | Wk 9-14 | |

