Based on the baseline characteristics of our former conducted comparable study75 with a subanalysis of women with a BMI >25 kg/m2 , for the SHAPE-2 study we assumed an average weight of 78 kg, length of 1.65 m and age of 58 years. This gives us a correction factor 1.376 for the standard METs resulting in MET rates of 11 METs for the aerobic training (8*1.376) and 8.3 METs for the strength training (6*1.376). This gives a total energy expenditure of 750 kCal per session (11*0.5*78 + 8.3*0.5*78).

The physiotherapist registers the attendance of the subjects. The study coordinator will perform several monitoring visits per exercise group.

Previous experience showed that group exercises are preferred in this age group and are better adhered to in the short and long term76(see also Preliminary results). For feasibility reasons, individual home-based exercise is also included.

*Individual Exercise*

The home-based exercise programme comprised Nordic Walking at 75-85% of the maximum heart rate for two times 60 minutes per week. Energy requirements were assumed based on calculated corrected MET’s from Ainsworth.73, 74 It is comparible to study outcomes of Figard-Fabre et al.77 when a higher heart rate of 130/min is assumed for our training programme. For an average woman in our study one 60-minute session of Nordic Walking will comprise an energy expenditure of 515 kCal (6.6*1*78).

Women will receive Nordic Walking poles. Nordic Walking technique will be demonstrated and practised during a group exercise session. To increase the compliance of this individual programme, women will be stimulated to walk with other participants (walking buddy). And supervised group sessions by a sports instructor will be organized. Women have to record the intensity and duration of their weekly Nordic Walk session in an exercise log. Furthermore, women will be asked to wear an activity monitor during the individual exercise sessions: the Actigraph78 ([www.theactigraph.com](http://www.theactigraph.com/)). The physiotherapists will use the Actigraph to check duration, frequency and calorie expenditure of the individual training sessions. For women who do not appreciate Nordic Walking, we will design an alternative programme with the same energy expenditure (e.g. cycling; swimming etc).

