## Analysis

Our primary and secondary endpoints will be changes in sex steroid hormones, body composition and fitness during the study. If sex hormones are non-normally distributed, log transformations will be used for analyses. We will analyse the effects by linear regression analysis. We will compare the effects of the diet group versus the exercise group, the diet versus control, and exercise versus control. The main analysis will be performed according to the intention-to-treat principle, where outcomes for patients are analyzed by assigned treatment, regardless of the level of adherence. As a secondary analysis, adherence will be examined as a potential modifier of the intervention effects.

To explore whether changes in body fat (total, abdominal) mediates intervention effects on sex hormone levels, we examined the change in the measure of association pre- versus post adjustment for changes in body fat (in the linear regression model). If the adjustment attenuates the measure of association, then we consider this to be suggestive of mediation. Furthermore, the main effect of total body fat/ abdominal fat on changes in sex hormone levels will also be evaluated in the linear regression models, adjusting for the intervention assignment. This method is based on a paper of Kraemer et al86 which explains that a mediator must show a change during treatment, must correlate with the treatment assignment, and must have a main or interactive effect on the outcome.

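### Treatment is given in session groups (10 women in D, 5-6 in E) but the regression has no term for group, so the E versus D standard error is too small if outcomes correlate within groups

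*Protocol*

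**What the plan says.** Randomisation is of individual women, in blocks of 5 with stratification (Protocol section 5.2). Delivery differs by arm:

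- **D (section 3.2).** "Five group sessions: In these one-hour sessions, participants in this treatment arm will be trained for self-management of body weight reduction". Group size and leadership are given: "Group sessions will be conducted by a dietician using a structured curriculum in groups of 10 women". The purpose is stated: "Group sessions are supposed to provide a combination of social support and a healthy dose of competition". So is the interaction: "At each session, women review each others weight history and help each other generating strategies to cope with problems identified".
- **E (section 3.3).** "Twice a week the participants of the combined exercise- plus diet-induced weight loss group will gather for a supervised exercise session for 60 minutes", led by a physiotherapist, in a 14-week programme. On size: "The groups consist of 5-6 women". For the home sessions, "women will be stimulated to walk with other participants (walking buddy"). The dietary contacts listed for E are individual sessions, telephone calls and a food record.
- **C (section 3.4).** Telephone monitoring only during the study period.

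For the analysis, section 7.2 says: "We will analyse the effects by linear regression analysis". It covers E versus D, D versus C and E versus C by intention to treat. No group or therapist term, cluster-robust error, ICC or design effect appears in the protocol. Section 4.4 sizes E versus D at 85 evaluable women per arm and inflates only for drop-out (5%) and non-compliance or contamination (15%), to 104.

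**The concern.** Women who share a leader, a timetable and, in D, a format built on mutual help may end up more alike than women in different groups. The protocol's rationale is that hormones follow weight and fat loss, so similar weight loss within a group could carry over to the primary outcomes. A regression that treats all women as independent then understates the variance of an arm mean. It does so unequally, because groups are about 10 in D, 5-6 in E and absent in C.

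E versus D is where this matters most. It has the smallest expected difference (8%), it sets the sample size, and it is planned at a minimum of 80% power, so there is little reserve. The risks are an interval that is too narrow, a type I error above 5%, and power below plan once the standard error is corrected.

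**Working it through.** **1. Reproduce the plan's sample size.** Inputs from section 4.4: mean log estradiol 2.28, SD 0.44, changes of -12% (D) and -20% (E), 80% power, alpha 0.05 (taken as two-sided).

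Applying the changes to the log mean and rounding: 0.88 × 2.28 = 2.01, 0.80 × 2.28 = 1.82, difference 0.19.

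n per arm = 2 × [0.44 × (1.960 + 0.842)/0.19]² = 84.2, rounded up to 85, as stated.

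Inflation: 85/(0.95 × 0.85) = 105.3, close to the stated 104 (84 would give 104.0).

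The figure is that of independent observations, with a design effect of 1. Without rounding, the difference is 0.1824 and independence needs 92. Either way, 85 contains no allowance for clustering.

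**2. Design effect.** Group sizes m = 10 (D) and 5.5 (E, midpoint of 5-6). The ICC is an assumption, taken as equal in both arms with the total SD unchanged.

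- Design effect per arm = 1 + (m − 1) × ICC
- True SE / naive SE = √[(DE_D + DE_E)/2]
- Type I error of the naive test = 2 × [1 − Φ(1.960/ratio)]
- Power at 85 per arm with the correct SE = Φ(0.19/SE − 1.960), where SE = 0.44 × √[(DE_D + DE_E)/85]

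| ICC (assumed) | DE in D | DE in E | SE ratio | Type I error | Power at 85 per arm |
|---|---|---|---|---|---|
| 0 | 1.00 | 1.00 | 1.000 | 5.0% | 80% |
| 0.01 | 1.09 | 1.045 | 1.033 | 5.8% | 78% |
| 0.02 | 1.18 | 1.09 | 1.065 | 6.6% | 75% |
| 0.05 | 1.45 | 1.225 | 1.157 | 9.0% | 68% |

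Example at 0.05: √[(1.45 + 1.225)/2] = √1.3375 = 1.157, 1.960/1.157 = 1.695, two-sided p = 0.090.

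A simulation of two-sample t-tests with 85 women per arm (D: eight groups of 10 and one of 5; E: ten groups of 6 and five of 5) gave 5.1%, 5.6%, 6.5% and 9.0% for the same four ICCs.

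**3. Cost of correcting the interval.** The 104 women per arm form about 10 groups in D and 104/5.5 ≈ 19 in E, giving 9 and 18 between-group degrees of freedom. A Satterthwaite approximation at ICC 0.05 gives (1.45 + 1.225)²/(1.45²/9 + 1.225²/18) ≈ 23. The t quantile at 23 df is 2.069, and 2.069/1.960 = 1.055. Intervals widen by 1.033 × 1.055 = 1.09 at ICC 0.01 and by 1.157 × 1.055 = 1.22 at ICC 0.05, so about 9-22%.

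**4. How well the between-group variance can be estimated.** With θ = ICC/(1 − ICC), the ANOVA estimate is zero or negative with probability P[F < 1/(1 + mθ)], using F(9, 90) for D and about F(18, 85.5) for E. For ICC 0.01, 0.02 and 0.05 this is about 48%, 41% and 25% in D, and 47%, 42% and 28% in E.

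**The case against.** The strongest objection is that section 7.2 names only a model family. It does not exclude a random intercept or robust errors, and such detail often sits in a statistical analysis plan, which is not shown here. That holds for the wording of the model. It does not hold for the sample size, which the protocol fixes and which already uses independence. The point therefore stands as an inexpensive improvement to a stated method, and omission of detail is not the complaint.

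Three stronger readings are tempting and are not supported:

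- **That groups are fixed.** The protocol gives sizes and does not say that membership is constant. Figure 1 places D's five sessions in weeks 7, 9, 11, 15 and 19, and E's training progresses by programme week. Both suggest groups that move together, but this remains an inference.
- **That peer influence is a stated mechanism in both arms.** It is explicit only for D. For E the protocol describes standardised sessions with individual heart-rate targets and loads, a shared physiotherapist, and encouragement to walk with others.
- **That hormone changes must be correlated within groups.** Several features work the other way. All women in D and E share a 5-6 kg target, those off the weekly goal for three weeks receive coaching or an adapted programme, weight loss stops at the individual goal, and each woman has individual sessions and calls. Hormones are a further step from weight. The ICC could be small, and at zero nothing changes.

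The remedy also has limits: the variance will often be estimated as zero, and the model then has the same point structure as the regression already planned. If women switch groups, a single-membership random intercept would be misspecified.

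**Conclusion.** The point holds conditionally. The protocol treats D and E in groups, leaves C ungrouped, and plans and sizes E versus D as if women were independent. If outcomes correlate within groups, the E versus D standard error is too small by a factor of about 1.03 at ICC 0.01 and 1.16 at ICC 0.05.

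This size rests on an ICC that no document supplies, on equal ICCs in D and E, and on stable membership. The effect is slight at the low end of the range, and the protocol does not establish that type I error is inflated. It does show that independence was assumed for an intervention which, at least in D, is designed to create dependence.

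The comparisons with control are affected too, but less, because the small ungrouped arm dominates the variance. For D versus C at ICC 0.05, (1.45/85 + 1/36)/(1/85 + 1/36) = 1.13, an SE ratio of 1.06. The matter merits a change to the analysis text and to data capture, and does not require redesign.

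**What to change.** 1. **Data capture.** Record each woman's session-group and therapist identifier in both D and E, and any change of group. Section 3.3 provides for the physiotherapist to register attendance in E. For D the protocol mentions only that reasons for absence are checked (section 6.3). Neither place mentions a group identifier. If it is not recorded, the correction may be impossible later.
2. **Section 7.2.** Pre-specify a partially nested version of the same regression, with an arm-specific random intercept for session group in D and E, controls ungrouped, and small-sample degrees of freedom. At minimum, make it a sensitivity analysis reported alongside the primary E versus D result. State what is done when the between-group variance is estimated as zero and when a woman changes group.

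The cost is some extra modelling, one or two extra data fields, and E versus D intervals about 9-22% wider at ICC 0.01-0.05 with roughly 23 degrees of freedom. With about 10 D and 19 E groups, the between-group variance will often come out as zero, so a null estimate should not be read as proof of independence. Treatment, visits and randomisation are unchanged.

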## Combined exercise- plus diet-induced weight loss (Group E)

Participants randomised to the combined exercise- plus diet-induced weight loss group will be enrolled in a 14 week structured exercise programme. Thereby, they follow an energy-restricted diet (which is less strict than for the diet-induced weight loss group). Goal of this combined programme is to produce a weight loss of 5-6 kg in total (approximately 0.5 kg per week) and to increase fitness. The weight reduction period, will be followed by a weight maintenance period of 2-6 weeks in which energy intake and energy expenditure will be balanced. The weight maintenance period starts as soon as the individual weight reduction goal is obtained (total weight loss of 5-6 kg), or in study week 19. Participants entering the maintenance period before week 19 will complete their 14 week exercise programme and can compensate correlated energy expenditure by increased caloric intake. From start of the maintenance period until end of study, energy intake should meet the individual energy requirements for weight maintenance.

Exercise Intervention

The 14 week exercise intervention programme creates an average energy expenditure of approximately 350 kCal/day. It consists of 2 one-hour supervised fitness group sessions at a physiotherapist centre. Plus 2 hours/week of individual home-exercise Nordic Walking. The training programme is a combination of high intensity endurance training and strength training. High intensity endurance training results in higher absolute fat oxidation rates than training of moderate intensity67. Knechtle and coworkers found that women’s fat oxidation rate was higher when cycling or running at 75% VO2peak than at 65% or 55% VO2peak. We choose for a combination with strength training since strength training is important for postmenopausal women to preserve and increase muscle mass and strength and to preserve bone mineral density68. Moreover, the advantages of strength training may have greater implications than initially proposed with respect to decreasing percentage body fat and sustaining fat free mass69. In addition, strength training might be helpful in combating the decrease in basal metabolic rate during the period of negative energy balance.

*Group Exercise*

Twice a week the participants of the combined exercise- plus diet-induced weight loss group will gather for a supervised exercise session for 60 minutes. The groups consist of 5-6 women. A physiotherapist who is extensively trained for the study will facilitate the standardised group sessions. Classes will start with a warming up. Then the training is continued with moderate-to-vigorous level of aerobic exercise (circuit training) on 60-90% of the peak heart rate (60-84% of VO2peak). The percentage of peak heart rate on which participants will train will increase gradually during the study programme (see table 1). The endurance training in week 9-14 will be a high-intensity interval training, with 30 seconds of intensive exercise and 60 seconds of active rest.  Exercise intensity was based on the guidelines of the American College of Sports Medicine, adapted for older woman70. Peak heart rate of each participant will be measured during a maximal exercise test. The participants will wear heart rate monitors to control their training intensity. They will also receive a badge with their target heart rates for a range of training intensities. The intensity and duration of the endurance training will be gradually inclined in the first weeks. Each training session will end with standardised strength exercises of the major muscle groups (see Tables 3a and 3b for an example of exercises; the type of exercise for a specific muscle group might be adapted to the facilities of the physiotherapist centre) and 5 minutes cooling down. The first week will be a run-in period for the strength exercises in which the technique of the exercises will be extensively instructed and practiced. Furthermore, in the first week the 20 repetition maximum (RM) (i.e. the maximum load that a muscle group can perform 20 repetitions of an exercise before becoming fatigued) will be determined for the different exercises (except for the abdominal exercises). This 20 RM will be the starting point for the strength training programme. To secure sufficient training load throughout the training programme, the 20 RM will be repeated at week 4; and a 15 RM will be determined at week 8 and 12.

Table 1. Content and composition of the group sessions

|  | **Time (min)** | **Intensity (% HF max for endurance part)** | | | | | |
| --- | --- | --- | --- | --- | --- | --- | --- |
|  |  | Phase 1 | | Phase 2 | | Phase 3 | |
| *Part of the session* |  | Wk 1-3 | | Wk 4-8 | | Wk 9-14 | |
| **Warming-up** | 5-10 | 60-65% | | 60-65% | | 60-65% | |
| **Endurance training** | 20-25 | 60-70% | | 70-80%  (5-10 min 80-90%) | | 70-90%  (high-intensity interval training; see table 2) | |
| **Strength exercises** | 25 | Increasing intensity and decreasing number of repetitions (see  Table 3a-b) | | | | | |
| **Cooling down** | 5 |  |  | |  | |  |

Table 2. High intensity endurance interval training during phase 3

| **Week** | Intensity | **Repetitions** |
| --- | --- | --- |
| 9 | 70% | 10 |
| 10 | 75% | 10 |
| 11 | 80% | 10 |
| 12 | 80% | 15 |
| 13 | 85% | 15 |
| 14 | 90% | 15 |

Table 3a. Strength exercises week 2-8

| **Muscle Group** | Exercise | **Intensity** |
| --- | --- | --- |
| Back | Rowing | 1x 20-25 reps |
| Chest | Bench press | 1x 20-25 reps |
| Legs (hips, glutes and thighs) | Squat | 1x 20-25 reps |
| Shoulder | Shoulder press | 1x 20-25 reps |
| Arms (biceps) | Bicepscurl | 1x 20-25 reps |
| Legs (hips, glutes and thighs) | Lunges | 1x 20-25 reps |
| Legs (calfs) | Calf-raises | 1x 20-25 reps |
| Arms (triceps) | Triceps extension | 1x 20-25 reps |
| Abdominal | Crunch | 1x 30-40 reps |

Table 3b. Strength exercises week 9-14

| **Muscle Group** | Exercise | **Intensity** |
| --- | --- | --- |
| Back | Rowing | 2x 15-20 reps |
| Chest | Bench press | 2x 15-20 reps |
| Legs (hips, glutes and thighs) | Squat | 2x 20-25 reps |
| Shoulder | Shoulder press | 2x 10-15 reps |
| Arms (biceps) | Bicepscurl | 2x 20-25 reps |
| Arms (triceps) | Triceps extension | 2x 20-25 reps |
| Abdominal | Crunch Hoover | 2x 30-50 reps |

The energy requirements of a group exercise session is based on the compendium of physical activities of Ainsworth et al71, 72.

In this compendium average metabolic equivalent (MET) rates are given. Since we have a specific study group of overweight and obese, sedentary postmenopausal women we calculated energy expenditure with the help of corrected MET’s specific for this population. Corrected MET’s can be calculated with the use of the Harris-Benedict formula.73, 74

We calculated a correction factor of 1.376

Based on the baseline characteristics of our former conducted comparable study75 with a subanalysis of women with a BMI >25 kg/m2 , for the SHAPE-2 study we assumed an average weight of 78 kg, length of 1.65 m and age of 58 years. This gives us a correction factor 1.376 for the standard METs resulting in MET rates of 11 METs for the aerobic training (8*1.376) and 8.3 METs for the strength training (6*1.376). This gives a total energy expenditure of 750 kCal per session (11*0.5*78 + 8.3*0.5*78).

The physiotherapist registers the attendance of the subjects. The study coordinator will perform several monitoring visits per exercise group.

Previous experience showed that group exercises are preferred in this age group and are better adhered to in the short and long term76(see also Preliminary results). For feasibility reasons, individual home-based exercise is also included.

*Individual Exercise*

The home-based exercise programme comprised Nordic Walking at 75-85% of the maximum heart rate for two times 60 minutes per week. Energy requirements were assumed based on calculated corrected MET’s from Ainsworth.73, 74 It is comparible to study outcomes of Figard-Fabre et al.77 when a higher heart rate of 130/min is assumed for our training programme. For an average woman in our study one 60-minute session of Nordic Walking will comprise an energy expenditure of 515 kCal (6.6*1*78).

Women will receive Nordic Walking poles. Nordic Walking technique will be demonstrated and practised during a group exercise session. To increase the compliance of this individual programme, women will be stimulated to walk with other participants (walking buddy). And supervised group sessions by a sports instructor will be organized. Women have to record the intensity and duration of their weekly Nordic Walk session in an exercise log. Furthermore, women will be asked to wear an activity monitor during the individual exercise sessions: the Actigraph78 ([www.theactigraph.com](http://www.theactigraph.com/)). The physiotherapists will use the Actigraph to check duration, frequency and calorie expenditure of the individual training sessions. For women who do not appreciate Nordic Walking, we will design an alternative programme with the same energy expenditure (e.g. cycling; swimming etc).

In conclusion, the exerciseprogramme, containing 2 hours of fitness training and 2 hours of Nordic walking, gives a total energy expenditure of 2530 kCal/week (2*750 + 2*515) for a modal participant. Resulting in an average energy expenditure of 360 kCal/day.

Procedures to enhance adherence to the exercise programme are: (1) use of group exercise sessions in combination with a simple individual programme, (2) personal feedback of the physiotherapists, (3) use of exercise logs and an activity monitor (4) stimulate women to find a walking buddy for the individual part, and (5) newsletters.

Diet Intervention

Next to the exercise programme, women enrolled in the combined exercise- plus diet-induced weight loss group will be prescribed an energy-restricted diet creating an extra energy deficit of 250 kcal/day during the weight reduction period of 10-14 weeks. Diet composition and recommendations will be comparable to the baseline diet.

The diet intervention consist of two individual 30 minutes individual sessions with a dietician, 7 telephonic contacts and completion of a food-record. Purpose and content of these contacts are similar as for the diet-group, described in paragraph 3.2.

Participants, whose weekly weight loss does not meet or exceeds the 0.5 kg/week goal for 3 consecutive weeks, will receive extra coaching and/or their programme will be adapted. Participants, who reach the individual weight reduction goal (weight loss of 5-6 kg) before week 14, will enter the weight maintenance period in which energy intake and energy expenditure will be balanced (i.e. they keep exercising but their diet will be adapted).

